### Randomisation and blinding

As we will be testing the feasibility of delivering a stepped wedge cluster design, the four different antenatal clinics will be randomised with two sites starting first (creating the first sequence) and two starting 6 weeks later (the second sequence). Randomisation will be performed by the study statistician who will generate a randomisation list using software and apply it to the pre-concealed list of clinics. The researchers and participants will not be blinded to whether they are in the intervention or the control cohort.

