**Methods:**

This protocol is for a study to examine the feasibility of undertaking a stepped wedge trial to test how a Community Health Intervention through Musical Engagement (CHIME) could be beneficial in alleviating perinatal mental distress in The Gambia. In this study, we plan to recruit 120 pregnant women (*n* = 60 intervention, *n* = 60 control) at four antenatal clinics over two 6-week stepped sequences. Women in the intervention will participate in weekly group-singing sessions, led by local Kanyeleng singing groups, for 6 weeks. The control group will receive standard care. We will assess symptoms of anxiety and depression using the Edinburgh Postnatal Depression Scale (EPDS) and the Self-Reporting Questionnaire (SRQ-20). The feasibility of the design will be assessed through recruitment, retention and attrition rates of participants, clinics' adherence to the schedule and completeness of data by site. Qualitative interviews and video and audio recordings will be used to evaluate the acceptability of the intervention.

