### Study population

All participants will be Mandinka or Wolof Gambian women who are pregnant.

Inclusion criteria
Pregnant (14–24 weeks gestation)Speak Wolof or Mandinka fluently

Exclusion criteria
At least one previous late term miscarriageCurrent psychosis or history of psychosis

Withdrawal criteria

If the participant develops any serious medical condition or the participant’s mental health significantly declines (as assessed by the care team), and the care team deem it necessary, then she may be withdrawn from the study.

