### Recruitment

Four antenatal clinics will be chosen to take part in the study based on three criteria: (1) availability of a local Kanyeleng group to deliver the intervention, (2) the language group predominantly spoken in the area (with at least one clinic being in a predominantly Wolof speaking area) and (3) the type of community the clinic serves (with at least one within an urban area).

The health professionals working at the health centre will first approach participants for the study. If they meet the criteria, they will be given information about the study and asked if they would like to be referred to the RAs. They will then be put in contact with one of the RAs who will meet them privately face to face. The information sheet will be read out in their native language verbatim to ensure participants’ ability to give informed consent. Consent will be taken orally by the RAs and recorded by signature or thumbprint. If participants do not choose to take part we will record their reason, if it is given, to help understand why women might not want or be able to participate.

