### Trial schedule

This trial design involves a sequential crossover of clusters whereby each cluster (antenatal clinic) receives the control condition followed by the intervention condition. The four chosen clinics will be randomised to two sequences of a 12-week phase. A separate cohort of participants will be recruited to the control group and the intervention (singing) group. Each cohort will be recruited around 4–6 months into their pregnancy. The 12-week phase for both the control and intervention cohort will include data collection at week 1 (“baseline”) and week 7 (“post”) after either group-singing (intervention) or standard care (control) as well as at week 11 (“follow-up”), 4 weeks after the intervention finished. Contamination will be avoided by having data for the control group collected before the intervention groups start at each clinic. See Fig. 1 for a schematic for the study.

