### Analysis

All data will be entered into a database by an RA and verified by the second RA using double data entry to ensure data quality. As this is a feasibility study, we will examine missing data as an outcome.

Descriptive statistics will be summarised to understand the demographic variables relating to the recruited population. Descriptive statistics and plots will be used to assess the distribution of the measurement tools, repeated at baseline and follow-up and by each arm. We will also examine the distributions of scores in the different language groups to see to what extent item scores and overall distributions differ or are similar. Correlations between our two measurement tools will be calculated.

To determine if the intervention is deliverable, we will record the number of sessions that the Kanyeleng groups delivered, aiming to deliver two thirds of the sessions, and the duration of each session, aiming to last between 45 and 75 min. We will also perform a qualitative evaluation, using the video and audio recordings, to determine intervention fidelity at the four sites. Both RAs will watch the video and audio recordings of the first and fourth group-singing sessions at each clinic and complete a checklist to determine if all the necessary elements—as outlined in the training workshops—were included in the intervention. Reliability of the fidelity measure will be ascertained by measuring inter-rater consistency.

We will also calculate the proportion of clinics approached that consented, aiming to reach over 50% recruitment rate, and record any scheduling problems in keeping with the stepped wedge timeline. Recruitment, adherence and completeness of data will be calculated for both groups. We aim to achieve a 60% recruitment rate and no more than 30% attrition in both arms. To determine if the intervention was culturally appropriate and well received by the community and health workers, we will collect qualitative data from post-intervention interviews and perform a thematic analysis.

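### Control then singing cohorts, recruited in a known order by unblinded staff-led approach, leave recruitment rate and case mix by arm open to selective approach

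*Protocol article*

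**What the plan says.** All references are to the protocol article.

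- **What is randomised.** Randomisation and blinding: "the four different antenatal clinics will be randomised with two sites starting first (creating the first sequence) and two starting 6 weeks later". No woman is randomised.
- **Order and cohorts.** Trial schedule: "each cluster (antenatal clinic) receives the control condition followed by the intervention condition", and "A separate cohort of participants will be recruited to the control group and the intervention (singing) group".
- **Blinding.** Randomisation and blinding: "The researchers and participants will not be blinded to whether they are in the intervention or the control cohort".
- **First contact.** Recruitment: "The health professionals working at the health centre will first approach participants for the study". Interested women who meet the criteria are then referred to a research assistant. If a woman declines, her reason is recorded when she gives one.
- **Eligibility.** Study population: 14 to 24 weeks' gestation, a window 10 weeks wide.
- **Use of the figures.** Objectives: the recruitment rate to each of the two groups is to be assessed. Analysis: "We aim to achieve a 60% recruitment rate and no more than 30% attrition in both arms", with the distributions of the two questionnaires described by arm. Sample size: pilot efficacy data and a standard deviation are to be carried into the definitive trial.

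**The concern.** Concealing the clinic list protects the order of the clinics. It does nothing for the women, because the next woman's arm can be read from the calendar. The people who decide whom to approach work in the clinic where the singing takes place, and a community health nurse there takes attendance, so they can be expected to know which cohort is being filled.

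Staff might approach women more freely in one period, or might approach those thought likely to enjoy singing or to need it. The proportion consenting among those approached would then differ between cohorts even if willingness in the clinic population were the same. Baseline symptom scores, adherence and attrition could differ for the same reason. The definitive trial would take over these figures without a way to separate true willingness from who was asked.

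**Working it through.** **1. What fixes a woman's arm.** Taken together, Randomisation and blinding, Trial schedule and Recruitment give: clinic order random; control before singing at every clinic; different women in each cohort; researchers and participants unblinded; first approach by clinic staff. Recruitment period is then the only route to an arm. The article does not say this in so many words, but its description leaves no other route. The one protection given in Trial schedule, collecting control data before singing starts, is aimed at contamination and does not address selection.

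**2. The plan's own precision figure.** Sample size claims ±9 points for binary feasibility outcomes. The half-width is 1.96 × √(p(1−p)/n). With p = 0.5 and n = 120 this is 1.96 × √(0.25/120) = 8.95 points, so the figure is reproduced with both arms pooled and clustering ignored. With n = 60 per arm it is 12.65 points. For the recruitment rate the denominator is women approached: 60 recruits at 60% means 60/0.6 = 100 approached per arm, and 1.96 × √(0.24/100) = 9.6 points. All of these measure sampling error only. None covers selection in who is approached.

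**3. Could the same woman wait for singing?** Let g be the weeks between a clinic's control and singing recruitment. She can wait only if her gestation at the control approach is at most 24 − g weeks. If gestation is spread evenly over the window (an assumption), the share able to wait is max(0, (10 − g)/10).

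| Gap g | Latest gestation able to wait | Share of window |
|---|---|---|
| 6 weeks | 18 weeks | 40% |
| 7 weeks | 17 weeks | 30% |
| 10 weeks | 14 weeks | 0% |
| 12 weeks | none (limit would be 12 weeks) | 0% |

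The document does not settle g:

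- The Abstract speaks of recruitment "over two 6-week stepped sequences", without defining a gap within a clinic.
- The 6 weeks in Randomisation and blinding is the offset between the two pairs of clinics.
- Trial schedule gives each cohort a 12-week phase with data at weeks 1, 7 and 11, and places control data collection before singing starts at that clinic. If week 11 is included, g is at least 11 − 1 = 10 weeks and waiting is essentially ruled out. If only the week 7 data are meant, g is about 6 to 7 weeks.

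These gaps run from baseline to baseline and assume a similar lead time from approach to baseline in both cohorts. The schematic (Fig. 1) was not available for this review and may settle the matter.

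**4. Would the planned records reveal selection?** Only in part. Reasons for refusal come from women who were approached and chose to explain. Demographic data come from participants. A woman whom staff never approach leaves no trace in either.

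**The case against.** The study is not designed to assess efficacy, the analysis by arm is descriptive, and recruitment under open conditions is one of the things it sets out to learn. A difference between arms would itself be a finding. Gestation, parity and regular musical engagement are collected from participants, so some imbalance would show. The blinding sentence concerns knowledge of one's own cohort and does not say that cohort is disclosed before consent. Consecutive approach and screening logs are also details that an article often leaves to the full protocol.

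Much of this limits the consequences, and it rules out stating distortion as fact. It does not remove the point. The outputs at risk are feasibility outputs, and a difference between arms is informative only if willingness can be told apart from selective approach. The problem lies in a stated combination of fixed order, open cohorts and staff-led approach. If the full protocol already contains a consecutive-approach rule, the point is met.

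A reader might go further and infer that women will decline control and wait for singing, so that the control rate falls below 60% while the singing rate rises. The document does not support this:

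- It needs a gap under 10 weeks, and the 6 weeks most readily cited separates pairs of clinics, not a clinic's two cohorts.
- No deferral rate is given, and nothing says that women who decline may be approached again or are told that singing will follow.
- Setting true willingness at exactly 60% makes any loss a miss. At 70%, with 40% able to wait and 25% of those doing so, control would read 70 − 70 × 0.40 × 0.25 = 63% and pass.
- The 60% is an aim, with no stop/go rule attached to it.

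**Conclusion.** The point holds as a risk of unknown size. Unblinded, staff-led recruitment into sequential cohorts in a fixed and known order allows selective approach. That can bias the recruitment rate and baseline case mix by arm, both of which the study intends to report or carry forward. This does not depend on the gap between cohorts. It rests on one inference, that clinic staff know which cohort is open.

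Whether a woman could wait for singing cannot be judged until the timing statements are reconciled. On the most direct reading of Trial schedule she essentially could not. No numerical distortion should be claimed. The point merits a change because the by-arm recruitment rate cannot otherwise be interpreted with confidence and the remedy is small.

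**What to change.** 1. Reconcile the Abstract, Randomisation and blinding, and Trial schedule so that the interval between a clinic's control and singing cohorts is stated once, including whether the week 11 control data precede the start of singing.
2. In Recruitment, have staff offer the study to all eligible women consecutively, in order of antenatal attendance, in both periods.
3. Keep a simple anonymous count of women eligible, approached and consented, per clinic and cohort. The difference between eligible and approached then shows selection that refusal reasons cannot.
4. Assign each woman to the cohort open when she is first approached. At the singing-period approach, ask whether she was approached before; anyone approached in the control period stays in the control denominator. Asking her directly avoids keeping names of women who did not consent. The article describes no identifiable approach list to check against, since it promises only decliners' reasons.
5. In Analysis, calculate the 60% recruitment target per cohort on this basis.

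The cost is a small amount of extra logging and possibly slightly slower filling of the singing cohort. Step 4 relies on women's recall, and it cannot detect a woman held back before any approach; the counts in step 3 show such women only in aggregate.

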### Outcome measurements

Two local research assistants (RAs) will collect all measures orally as there is a high rate of illiteracy among the target population. All scales have been translated into Mandinka and Wolof. The translation method used was based on suggestions by the World Health Organisation, Hanlon et al. [19] and Cox, Holden and Henshaw [20]. First, the scales were translated into Mandinka and Wolof. An expert panel discussion then refined the translation before back translating it into English. The expert panel came together once more to resolve any remaining issues before finalising the translation.

Two questionnaires will measure antenatal anxiety and depression symptoms. The Edinburgh Postnatal Depression Scale (EPDS) [21] is a ten-item scale that was developed to screen for postnatal depression. It has subsequently been validated to be used during pregnancy [22]. This measurement tool has been used and validated in other African contexts; however, there is no avaliable validated version of the EPDS in Mandinka or Wolof even though it has been used in The Gambia before [23]. The Self-report Questionnaire (SRQ-20) [24] is a 20-item scale developed by the World Health Organization to measure anxiety and depression symptoms in a variety of cultural contexts. It has been used in many different African contexts such as Ethiopia [19], South Africa [25] and Rwanda [26] and as a way to measure perinatal mental health [23]. However, the SRQ-20 has never been used in the Gambian context nor has it been translated into Wolof or Mandinka.

### Demographic outcomes

We will collect demographic information about all participants. The data we will collect is as follows: date of birth, gestational age, time taken to get to the health centre, parity, gravida, place of birth, current place of residence, ethnic group, history of serious illness, occupation, husband’s occupation, marital status, educational background and amount of regular musical engagement.

### Feasibility outcomes

The feasibility outcomes are as follows:
Recruitment rateRetention and attrition rates of participantsClinics' adherence to stepped wedge scheduleCompleteness of data by site and over timeVideo and audio recording of sessions to determine fidelity of the intervention at each site, i.e. whether key content emphasised in training workshops was being delivered at each site.Qualitative interviews with participants after the intervention to capture enjoyment and perceived benefit.

### Recruitment

Four antenatal clinics will be chosen to take part in the study based on three criteria: (1) availability of a local Kanyeleng group to deliver the intervention, (2) the language group predominantly spoken in the area (with at least one clinic being in a predominantly Wolof speaking area) and (3) the type of community the clinic serves (with at least one within an urban area).

The health professionals working at the health centre will first approach participants for the study. If they meet the criteria, they will be given information about the study and asked if they would like to be referred to the RAs. They will then be put in contact with one of the RAs who will meet them privately face to face. The information sheet will be read out in their native language verbatim to ensure participants’ ability to give informed consent. Consent will be taken orally by the RAs and recorded by signature or thumbprint. If participants do not choose to take part we will record their reason, if it is given, to help understand why women might not want or be able to participate.

### Incentive and participant retention

Participants in both groups will be offered a total of 600 Dalasi (about 12 USD) for their time, 200 Dalasi for each of the three data collection time points (baseline, post, follow-up). All participants will be reminded of the data collection and the group-singing sessions by phone call. Calls will be made by the RAs 3 days and 1 day before as well as on the day of these appointments. Where possible, a record will be kept of the reasons women give for failing to join the intervention or data collection session.

### Sample size

As this is a feasibility study, it is not designed to assess the efficacy of the intervention, although pilot data on this will be collected. We will evaluate the feasibility of study design, data collection and whether the intervention is deliverable and acceptable to the participants. In the study, we will gather information to be used in the design of the future definitive study including an estimate of the standard deviation of potential primary outcomes to inform the sample size. We aim to collect data from a total of 120 pregnant women, 60 in the control condition and 60 in the intervention condition [27]. This number will be sufficient to provide estimates of binary feasibility outcomes with precision of at least ± 9 percentage points for the 95% confidence interval.

### Trial schedule

This trial design involves a sequential crossover of clusters whereby each cluster (antenatal clinic) receives the control condition followed by the intervention condition. The four chosen clinics will be randomised to two sequences of a 12-week phase. A separate cohort of participants will be recruited to the control group and the intervention (singing) group. Each cohort will be recruited around 4–6 months into their pregnancy. The 12-week phase for both the control and intervention cohort will include data collection at week 1 (“baseline”) and week 7 (“post”) after either group-singing (intervention) or standard care (control) as well as at week 11 (“follow-up”), 4 weeks after the intervention finished. Contamination will be avoided by having data for the control group collected before the intervention groups start at each clinic. See Fig. 1 for a schematic for the study.

**Fig. 1 Fig1:**
[figure not shown]
Schematic of the study

### Assessment and management of risk

There are no high risks within our study compared to standard care. We have identified three areas of ethical concern and have outlined how each of these issues will be managed.
Mothers may experience an adverse effect such as a miscarriage, difficult birth, still birth, a sudden drastic change in physical or mental health, infant health problems or even a serious adverse effect such as death during the intervention. It is possible that a participant experiencing such an adverse event may attribute a causal link between the adverse event and their involvement in the study. We will mitigate this association being made, firstly, by clearly explaining the nature of the intervention and any possible risks to the women when they are recruited into the study. If, despite this, an association of this nature was still made, we would enlist the help of the Ministry of Health & Social Welfare (our partner on the project) to disseminate information to the women and the community concerning the incidence of such events occurring in the general population in an attempt to reassure those concerned that such adverse events should not be attributed to involvement in the study.It is possible that some of the themes involved in questionnaires could lead to the women revealing episodes of self-harm. If this is the case, the woman will receive in the moment front-line counselling to talk through these issues with the RAs who are trained psychiatric nurses. Then, if needed, she will be referred on to the community mental health team (CMHT) for further management. If the CMHT deems it appropriate, they may then refer her on to the psychiatric team.It is possible that some of the themes involved in questionnaires may also lead the women to reveal domestic abuse. If this is the case, the woman will receive in the moment front-line counselling to talk through these issues with the RAs. For emergencies and cases that require immediate intervention, the RAs will connect with the Gender-Based Violence focal person. For other cases, the RAs will refer the woman to the One Stop Center at Serekunda General Hospital or Edward Francis Small Teaching Hospital.Women throughout the study will be monitored by the RAs, both trained psychiatric nurses. If the RAs feel that at any point a woman’s score indicates a high level of symptoms and/or the women reveal that they are particularly struggling, the RAs will refer the woman on to the Community Mental Health Team (CMHT) for further management. If the CMHT deems it appropriate, they may then refer her on to the psychiatric team.
